## Phase 2: intervention, adaptation, implementation, and Analytic Plan (n = 80)

4

During Phase 2, we will complete Aim 2a and 2b of the study, which focuses on exploring the feasibility, satisfaction, and plausibility (i.e., preliminary efficacy) of a sleep intervention designed to increase sleep duration and physical activity (PA). This phase employs a 6-week randomized controlled trial (RCT) to evaluate the intervention compared to a contact control group (see Fig. 1). Phase 2 involves a 7-day baseline assessment, followed by a 4-week intervention period, and concluding with a 7-day follow-up assessment. Eligible participants will be randomly assigned to one of two conditions: a sleep extension intervention or contact control. The primary goal of the sleep intervention is to increase sleep duration by 1 h over the course of four weeks and improve PA.

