**Fig. 1 fig1:**
[figure not shown]
Aim 2 sleep intervention randomized control trial design. *∗*Measurement of metabolic (insulin, adiponectin, leptin) and pro-inflammatory (IL-6, CRP, TNF-α).

**Interventions.** The sleep extension intervention is designed for AA adults who habitually obtain insufficient sleep, regardless of sleep disorder status, and aims to increase nightly sleep duration and daily physical activity. While sleep duration is a primary target for preliminary efficacy, we include physical activity based on prior research indicating the reciprocal relationship between sleep and physical activity (see *Introduction*). The intervention adapts selected components of Cognitive Behavioral Therapy for Insomnia (CBT-I) [79], including psychoeducation and stimulus control, while intentionally excluding sleep restriction. Participants receive four weekly one-on-one sessions via Zoom, delivered by trained study staff following a standardized protocol. Interventionists include master's-level counseling psychology graduate students trained in behavioral sleep principles and community engagement. Sessions follow a structured framework. Session 1 (60 min) introduces foundational sleep health concepts, including psychoeducation on the physiological and cognitive impacts of insufficient sleep, relaxation training, and individualized goal setting for bedtime extension. Sessions 2–4 (30 min each) involve review of weekly sleep diaries, monitoring of adherence to incremental bedtime targets (e.g., 15-min weekly increases), identification of barriers, and reinforcement of sleep-promoting behaviors such as consistent wake times and reduced evening screen use. Culturally relevant strategies—such as faith-based wind-down routines and household sleep negotiations—are integrated based on participant context. Tailored home practice recommendations, including relaxation exercises, are also provided weekly. Participants are encouraged to maintain their extended sleep schedule during the follow-up week. The intervention does not include any content related to physical activity promotion or goal-setting. However, physical activity is assessed as a secondary, non-targeted behavioral outcome to examine whether increasing sleep duration may be associated with incidental changes in activity levels.

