The structure of the intervention limited to 4 sessions was based on a meta-analysis of 87 CBT-I randomized controlled trials (RCTs), which concluded that a minimum of 4 sessions was necessary for meaningful improvements in sleep outcomes compared to self-help interventions or fewer sessions [80]. Further, evidence suggests that short, pragmatic community-based workshops can significantly improve sleep efficiency and reduce insomnia symptom severity [81], reinforcing the potential effectiveness of a brief intervention approach. However, given that this intervention targets insufficient sleep rather than clinical insomnia, its structure reflects a pragmatic adaptation aimed at improving sleep duration in a population that may not necessarily meet diagnostic criteria for insomnia.

The contact control condition is based on the National Center for Healthy Housing's Healthy Homes program, designed to control for time, engagement, and participant interaction with study staff. Participants in this group will receive four weekly Zoom sessions (15–30 min each) covering topics such as indoor air quality, emergency preparedness, pest control, injury and fall prevention, and poison control. The sessions parallel the sleep intervention in frequency and duration but focus on home health education rather than sleep behavior change. Staff will also check in on participants' progress in applying the educational content and address any challenges.

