**Training, Supervision, and Fidelity Monitoring.** All counselors delivering the interventions are graduate students in counseling or clinical psychology with prior clinical experience and foundational training in psychotherapy theories. The study PI (IW), a trained clinical psychologist with formal training in CBT-I, will oversee counselor training and supervision. Interventionist training is delivered across three structured sessions and covers: (1) the theoretical framework and content of the sleep extension intervention, (2) delivery of the contact control (Healthy Homes) condition, and (3) use of REDCap for intervention delivery, data entry and fidelity tracking. Training includes didactic instruction, in-session modeling, and supervised practice of all intervention components. Counselors also conduct mock sessions with test cases and in-person rehearsals with the PI prior to implementation. Counselors attend weekly team meetings for supervision, where they will present and receive individualized case feedback from the PI. Supervision focuses on reviewing participant progress, identifying barriers to implementation, and ensuring intervention adherence. All intervention sessions will be audio-recorded (with participant consent), and a subsample reviewed periodically by the PI. Fidelity is monitored using a REDCap-based session checklist that tracks delivery of core content and session structure. Each session will be scored based on the percentage of protocol elements delivered, with a threshold of ≥80 % considered acceptable fidelity. If a counselor delivers fewer than 80 % of required elements in more than one reviewed session, they will receive targeted retraining. Retraining will include direct supervision with the PI, review of fidelity checklists, and additional roleplay-based practice on missed intervention components.

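### The control sessions are described as parallel in duration to the sleep sessions, but the scheduled session time is 60–120 min against 150 min

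*Protocol article*

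**What the plan says.** All of this stands in Section 4 (Phase 2) of the protocol article.

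- **Sleep arm (Interventions).** There are four weekly one-on-one Zoom sessions. The lengths are given as "Session 1 (60 min) introduces foundational sleep health concepts" and "Sessions 2–4 (30 min each) involve review of weekly sleep diaries".
- **Control arm (Interventions, contact control).** The condition is "designed to control for time, engagement, and participant interaction with study staff". Participants receive "four weekly Zoom sessions (15–30 min each"). The next sentence claims parity: "The sessions parallel the sleep intervention in frequency and duration but focus on home health education rather than sleep behavior change". The paragraph closes by saying that staff will also check on participants' "progress in applying the educational content and address any challenges". No minutes are given for this.
- **Programme length (opening paragraph of Section 4).** Baseline is "followed by a 4-week intervention period, and concluding with a 7-day follow-up assessment", the same in both arms.

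No total contact time is stated for either arm.

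**The concern.** A contact control is there to remove the non-specific effect of staff time and attention from the between-arm comparison. The article says so and then says that its sessions match in duration. The minutes printed immediately before that statement are shorter than those of the sleep arm.

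At stake is how the between-arm effect sizes for sleep and physical activity are read. The Analytic plan will report them with 95% confidence intervals, and the Discussion intends them to inform the design of a later efficacy trial. Some of the outcomes are self-reported, so extra staff attention could plausibly move them. A reader who relies on the parity sentence would take session time as held equal between arms when it is not.

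**Working it through.** **Inputs**, all from Section 4, Interventions:

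- Sleep arm: session 1 is 60 min; sessions 2, 3 and 4 are 30 min each.
- Control arm: four sessions of 15 to 30 min each.

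The article gives no total, so there is no stated figure to reproduce. The check is a sum of scheduled lengths.

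**Total scheduled session time per participant**

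- Sleep arm: 60 + 3 × 30 = 150 min.
- Control, shortest: 4 × 15 = 60 min, and 60/150 = 40%.
- Control, longest: 4 × 30 = 120 min, and 120/150 = 80%.
- Gap: 150 − 120 = 30 min to 150 − 60 = 90 min.

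**By session**

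| | Sleep arm | Control | Gap |
|---|---|---|---|
| Session 1 | 60 min | 15–30 min | 30–45 min |
| Sessions 2–4 together | 3 × 30 = 90 min | 3 × 15 = 45 to 3 × 30 = 90 min | 0–45 min |
| Total | 150 min | 60–120 min | 30–90 min |

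The ranges for session 1 do not overlap. For sessions 2–4 there is equality at one point only, where every control session runs its full 30 min.

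**Could the check-ins close the gap?** The text does not say whether they take place inside or outside the sessions. If outside, they would have to supply 30–90 min over four weeks, that is 30/4 = 7.5 to 90/4 = 22.5 min a week, to equalise staff time. Even then the sessions themselves would differ in length, and session length is what the sentence describes.

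**What does match.** Four sessions in each arm, weekly, by Zoom, over the same four weeks.

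**The case against.** Three arguments on the other side deserve weight.

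*Duration may mean programme length.* The sentence compares the sessions with the sleep intervention as a whole, and *parallel* is looser than *equal*. Four weekly sessions over four weeks do match in that sense. But the subject of the sentence is the sessions, their minutes stand in the sentence just before, and the paragraph opens by saying that the condition controls for time. If programme length was meant, the wording still conveys matched session time and needs changing.

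*The consequence is small.* This stands. Feasibility is judged on attendance in the sleep arm against a fixed 75%, and satisfaction against a fixed mean score of 20. Neither depends on the control's session length. The study reports no p-values, and its between-arm results are descriptive. Both sets of minutes are printed, so an attentive reader can see the difference. No sample size, threshold or decision rule changes.

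*Session minutes are not staff contact.* This also stands. A reader might infer that control participants get only 40–80% of the staff contact. The document does not support that: check-in minutes are unstated, and both arms also have in-person visits, reminders and follow-up communications. The percentages apply to scheduled session time alone.

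A reader might also infer that the effect sizes are biased by the whole gap. That goes too far as well. Part of the longer first session is active treatment (psychoeducation, relaxation training and goal setting), so not all of the extra time is non-specific attention. The size of any attention effect cannot be computed from the document.

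**Conclusion.** Wrong as written, minor severity. The article claims a design property, matched session duration, that its own listed lengths do not give. Scheduled session time in the control is 30–90 min shorter per participant. Session 1 differs under any permitted schedule, and sessions 2–4 differ unless each control session runs to its maximum.

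The conclusion rests on reading *duration* as session length and on taking the printed minutes as the schedule. It assumes nothing about what will be delivered in practice or about total staff contact.

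The practical effect is limited to interpretation. The descriptive between-arm effect sizes for sleep and physical activity can be said to control for number, frequency and mode of sessions, but not fully for session time. The primary feasibility and satisfaction conclusions do not depend on this.

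**What to change.** **Reword the sentence.** For example: *The sessions match the sleep intervention in number, weekly frequency and mode (Zoom); scheduled session time is shorter (60–120 against 150 min), so session time is not fully matched.* This costs a text edit.

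**Report delivered session minutes by arm** beside the between-arm effect sizes. The fidelity checklist in REDCap is described as tracking content and structure, with no mention of minutes, so one field may need to be added. The recordings should not be relied on for this. The article says "All intervention sessions will be audio-recorded (with participant consent), and a subsample reviewed periodically by the PI", which makes recording subject to consent and leaves it unclear whether control sessions are included.

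**Optional and costlier alternative.** Set the control sessions to 60 + 3 × 30 min and keep the claim. For 40 control participants this adds 40 × 30/60 = 20 to 40 × 90/60 = 60 participant hours. It adds the same number of counselor hours if control sessions are delivered one-on-one, which the article does not state. It also needs more Healthy Homes content: 30–45 min in session 1 and up to 45 min over sessions 2–4. For a pilot with descriptive between-arm results, the rewording is enough.

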## Methods

2

**Overview*.*** Phase 1 focuses on conducting in-depth qualitative interviews to gain insights into sleep-related social contextual factors, knowledge, behaviors, and beliefs. This phase aims to gather feedback on the existing sleep intervention design and materials, ensuring they are culturally relevant and tailored to the needs of the community. Interviews will be conducted via Zoom to increase accessibility for participants. The collected data will help contextualize the lived experiences of the participants and inform the intervention to be implemented in Phase 2. Phase 2 involves a randomized controlled trial (RCT) to evaluate the feasibility, satisfaction, and preliminary efficacy of the sleep intervention compared to a contact control group. Eligible participants will be randomly assigned to one of two 4-week treatment conditions: the sleep extension intervention or the contact control. The sleep extension intervention aims to increase sleep duration by 1 h over four weeks, using components from CBT-I. Both intervention and control sessions will be conducted via Zoom. Based on recommendations for maintaining intervention fidelity [73], we will create an intervention manual, establish training and supervision protocols, and monitor both intervention delivery and participant engagement. We will regularly analyze fidelity data, provide corrective feedback, and document any deviations from the protocol to ensure the intervention is delivered as intended.

**Setting.** The study will be conducted in collaboration with Progressive Missionary Baptist Church in St. Paul, Minnesota, with all participant recruitment and in-person study activities occurring at this site, except for blood draws, which will take place at a university-affiliated facility. Phase 1 qualitative interviews and the 4-week intervention sessions for Phase 2 will be conducted virtually via Zoom to enhance accessibility. In Phase 2, baseline and follow-up assessments will be conducted in person at Progressive Missionary Baptist Church.

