A Community Advisory Board (CAB) will be established composed of congregation members from the community partner's church. The CAB will meet more frequently during the initial implementation phase and transition to quarterly meetings during the active intervention phase. The lead pastor will participate in quarterly study team meetings to ensure ongoing alignment with church priorities. Two congregation members will serve as core members of the research team and will attend all team meetings. They will provide real-time feedback during implementation planning and decision-making and will also assist in organizing and facilitating CAB activities. CAB members will review intervention materials, suggest culturally relevant adaptations, inform recruitment and retention strategies, and help interpret preliminary findings for community-facing dissemination. This structure will ensure sustained, bidirectional engagement and accountability between the academic and church partners across all phases of the study.

**Implementation (randomization and assessment periods).** At the end of the baseline visit, participants will be randomized into one of the two conditions using minimization randomization,{Scott, 2002 #129} taking into account participants’ sex assigned at birth. The baseline assessment includes a 7-day period where participants complete self-administered questionnaires, wear an accelerometer to monitor activity and sleep, and undergo a blood draw if they volunteer for this component (n = 20). After the 4-week intervention period, a follow-up assessment identical to the baseline assessment will be conducted. This includes completing questionnaires, wearing the accelerometer for another 7-day period, and undergoing a second blood draw for those who volunteered. Retention strategies include regular follow-up communications and reminders from the research team. Participants will receive financial compensation for their participation: a gift card for each in-person assessment visit ($50 for the baseline visit, $50 for the follow-up visit, and $50 for returning the actigraph watch). Those volunteering for blood draws will receive additional compensation ($40 for the first visit, $60 for the second visit).

**Measures.** Participants will complete both self-report questionnaires (e.g., measures of social contextual factors, psychosocial factors, and health behaviors), as well as physical measurements (e.g., anthropometric and blood draws).

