**Analytic plan.** Quantitative data from Phase 2 will be analyzed to assess feasibility, acceptability, and preliminary efficacy. Descriptive statistics, including means, medians, standard deviations, and 95 % confidence intervals (CIs), will be reported for sleep and PA outcomes. Pre-post changes will be examined for ceiling or floor effects and range restrictions. Graphs will visualize outcome distributions over time by group, highlighting differences in demographics and retention status.

While the power analysis was originally conducted for a repeated measures ANOVA, the primary analytic approach will use linear mixed models (LMMs) to account for repeated measurements and missing data. Given the exploratory nature of this pilot study, p-values will not be reported. Instead, standardized effect sizes (e.g., Cohen's d for between-group differences, standardized β coefficients from LMMs) will be reported with their standard deviations and 95 % CIs to evaluate trends and inform future trials.

LMMs will be used to examine within-group and between-group changes in primary outcomes (sleep quality, sleep duration, PA, and sedentary behavior) over the 4-week study period. While group differences over time will be explored, this study is not powered to detect interaction effects with high precision. Therefore, results will focus on descriptive effect size estimates rather than hypothesis-driven interaction testing. Analyses will follow the intention-to-treat (ITT) principle, ensuring that all randomized participants are included in analyses regardless of adherence. Missing covariate data will be handled via multiple imputation, while missing outcome data will be addressed using maximum likelihood estimation (MLE) within the LMMs. Baseline differences in participant characteristics and outcomes will be examined, with significant differences included as covariates to control for potential confounding. Loss to follow-up rates and differential attrition effects will also be evaluated.

For exploratory Aim 2b, changes in inflammatory and metabolic biomarkers (or their log transformations, if needed) will be described using means, standard deviations, and 95 % CIs to identify trends in proinflammatory and metabolic markers.

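### As written, randomization precedes the 7-day baseline actigraphy and apparently the first blood draw, so those baselines can be affected by knowledge of the arm

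*Protocol article*

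**What the plan says.** All references are to the protocol article.

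- **Time of allocation** (section 4, Implementation): "At the end of the baseline visit, participants will be randomized into one of the two conditions using minimization randomization", with sex assigned at birth as the minimization factor.
- **Content of the baseline** (same paragraph, next sentence): "The baseline assessment includes a 7-day period where participants complete self-administered questionnaires, wear an accelerometer to monitor activity and sleep", and participants also "undergo a blood draw if they volunteer for this component (n = 20").
- **Place** (section 2, Setting): "baseline and follow-up assessments will be conducted in person at Progressive Missionary Baptist Church", "except for blood draws, which will take place at a university-affiliated facility".
- **Payments, in dollars** (section 4, Implementation): "50 for the baseline visit, $50 for the follow-up visit, and $50 for returning the actigraph watch".
- **Sequence** (section 4, opening paragraph): "Phase 2 involves a 7-day baseline assessment, followed by a 4-week intervention period", then a 7-day follow-up.
- **Analysis** (section 4, Analytic plan): linear mixed models for within-group and between-group change in sleep, physical activity and sedentary behavior, following intention to treat, "ensuring that all randomized participants are included in analyses regardless of adherence". Missing outcomes are handled by maximum likelihood. Baseline differences found significant, including differences in outcomes, become covariates.

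**The concern.** A baseline can be relied on as a pre-treatment value only if it is recorded before the participant can react to the assigned arm. Here one arm works on sleep and the other on home health topics, so the assignment is obvious once disclosed. A participant who learns at the visit that they are in the sleep arm may go to bed earlier, or record sleep differently, in the week that is meant to show habitual sleep.

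Three things are at stake:

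- The pre-post contrasts for sleep and activity would start from a baseline that allocation may have altered.
- The plan would treat a significant baseline outcome difference as confounding and adjust for it, although it might be an effect of allocation.
- Watch return, dropout in that week and, if it is settled after the visit, volunteering for the blood draw could depend on arm.

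The trial is meant to supply effect sizes for a later efficacy trial, so a bias here would be carried forward.

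**Working it through.** **1. Order of events.** The article does not state in so many words that the watch is worn after the visit. The statements that bear on it are these.

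- Screening, consent and a first questionnaire are electronic, and the in-person baseline visit is scheduled afterwards (Recruitment and Eligibility Criteria). It is the first in-person contact described for Phase 2, and no mailing of watches is mentioned.
- One baseline visit and one follow-up visit are paid. No second baseline visit is described at which allocation could take place after the wear week.
- Return of the watch is paid separately, which fits a device issued at the visit and worn afterwards.
- Blood is drawn at a different site from the visit, so the draw is not part of it. A draw before the visit is not excluded, but none is described.
- The opening of section 4 and the Secondary outcomes paragraph place the week before the intervention, not before randomization.

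The natural reading is visit, then randomization, then the 7-day wear and probably the blood draw, then session 1.

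**2. How a shift propagates.** Let T be the true effect at follow-up and d the extra sleep in the sleep arm during the baseline week caused by knowing the arm.

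- Change from baseline (Time × Condition contrast): estimate = T − d.
- Follow-up adjusted for baseline, with equal variances and correlation r: estimate = T − r·d.
- Follow-up compared without use of baseline: estimate = T.

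Inputs: T = 60 minutes, the stated one-hour target; r = .50, the intra-class correlation in the sample size paragraph. **The article gives no value for d, so every value below is an assumption.** The 15-minute row equals one of the weekly bedtime steps that the intervention gives as an example.

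| Assumed d (min) | d / 60 | Change score, 60 − d | Baseline-adjusted, 60 − 0.5d |
|---|---|---|---|
| 0 | 0% | 60 | 60 |
| 6 | 10% | 54 | 57 |
| 15 | 25% | 45 | 52.5 |
| 30 | 50% | 30 | 45 |

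**3. The plan's own power figure.** After 12.5% attrition, 80 × 0.875 = 70. With f = .35 and noncentrality f²(N − 2) = 0.1225 × 68 = 8.33 on 1 and 68 degrees of freedom, power is 0.81, which matches the stated 80%. (Under a convention that credits the .50 correlation separately it exceeds 0.99; that is a different matter.) If the contrast shrinks by 10%, 25% or 50%, power on the matching convention falls to 0.73, 0.57 or 0.30. Because no p-values will be reported, this serves only as a scale for the loss of signal.

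**4. Intention to treat.** Maximum likelihood keeps a participant who has an actigraphy value at either time. It cannot use one who has none. The planned attrition is 80 × 0.125 = 10. The article does not say how much of it falls in the baseline week, so the number with no actigraphy for this reason could be anything from 0 to 10 of 80 within that allowance.

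**The case against.** Much can be said against a stronger version of this point, and most of it stands.

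- **Order and disclosure are inferred.** The text says when participants are randomized, not when they are told, and Figure 1 cannot be seen here. Psychoeducation and bedtime goals begin only in session 1, so during the baseline week a participant would know little more than the arm.
- **Not every baseline is affected.** A reader might infer that the diary and all questionnaires follow allocation. The sentence on the baseline week does not name the diary, one electronic questionnaire goes out with the consent form before the visit, and anthropometry is probably taken at the visit.
- **Not every estimate is a change score.** The Analytic plan also lists Cohen's d for between-group differences without saying that it is based on change. A comparison at follow-up alone would escape the bias.
- **No false signal of benefit follows from the obvious mechanism.** Early sleep extension in the sleep arm raises that arm's baseline and shrinks the estimated gain. A reaction in the control arm, or altered reporting, could move it either way, but the article gives no ground for expecting an inflated effect.
- **The study is a pilot.** It is not designed for formal hypothesis testing, and the biomarker work is descriptive in 20 volunteers. When they volunteer is not stated, so dependence on arm is only a possibility.

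These arguments limit scope, size and certainty. None supplies a statement that allocation is withheld or that the wear week comes first.

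**Conclusion.** The point holds in limited form. As the Implementation paragraph reads, randomization comes before the 7-day accelerometer baseline and apparently before the first blood draw, with no stated concealment of the result in between. The baselines at risk are actigraphic sleep and physical activity, and any diary, questionnaire or blood measure that is in fact taken after the visit.

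Any arm-specific shift enters a pre-post contrast in full and a baseline-adjusted one at about half, given a correlation of .50. The size of the shift is unknown. The likeliest direction is toward the null.

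It would be wrong to conclude that the intention-to-treat analysis fails as a whole: only participants with no actigraphy at either time are lost, and only for that outcome. Nor does the point touch the primary outcomes defined under Measures. Session attendance and satisfaction score use no baseline. The conclusion rests on two inferences: that the watch is worn after the visit, and that participants learn their arm when they are randomized.

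**What to change.** Perform randomization, or at least disclose its result, only after the 7-day wear, the remaining baseline measures and the first blood draw are complete, immediately before session 1. Record willingness to give blood before allocation. If disclosure alone is delayed, the staff who collect baseline data should not know the arm either. If this is already the practice, amend the Implementation paragraph to state the order and the time of disclosure.

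The cost is a change of wording and procedure, and a short delay in issuing allocation. Sessions are held by Zoom, so no extra visit is needed. The two options differ in one respect:

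- **Delayed randomization** keeps those who leave in the baseline week out of the randomized set, so slightly fewer than 80 are randomized unless they are replaced. For example, if 5 left (an assumption), 80 − 5 = 75 would remain.
- **Delayed disclosure** keeps 80 randomized. It leaves the gap in actigraphy for those who depart in that week, but their departure can no longer depend on knowing the arm.
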